## Abstract

**Introduction:**

Skin malignancy is a distressing problem for many patients, and clinical management is challenging. This article describes the protocol for the Calcium Electroporation Response Study (CaEP-R) designed to investigate tumour response to calcium electroporation and is a descriptive guide to calcium electroporation treatment of malignant tumours in the skin. Calcium electroporation is a local treatment that induces supraphysiological intracellular calcium levels by intratumoural calcium administration and application of electrical pulses. The pulses create transient membrane pores allowing diffusion of non-permeant calcium ions into target cells. High calcium levels can kill cancer cells, while normal cells can restore homeostasis. Prior trials with smaller cohorts have found calcium electroporation to be safe and efficient. This trial aims to include a larger multiregional cohort of patients with different cancer diagnoses and also to investigate treatment areas using MRI as well as assess impact on quality of life.

**Methods and analysis:**

This non-randomised phase II multicentre study will investigate response to calcium electroporation in 30 patients with cutaneous or subcutaneous malignancy. Enrolment of 10 patients is planned at three centres: Zealand University Hospital, University Hospital of Southern Denmark and University Hospital Schleswig-Holstein. Response after 2 months was chosen as the primary endpoint based on short-term response rates observed in a prior clinical study. Secondary endpoints include response to treatment using MRI and change in quality of life assessed by questionnaires and qualitative interviews.

**Ethics and dissemination:**

The trial is approved by the Danish Medicines Agency and The Danish Regional Committee on Health Research Ethics. All included patients will receive active treatment (calcium electroporation). Patients can continue systemic treatment during the study, and side effects are expected to be limited. Data will be published in a peer-reviewed journal and made available to the public.

**Trial registration numbers:**

NCT04225767 and EudraCT no: 2019-004314-34.

Strengths and limitations of this studyThis study investigates calcium electroporation as a novel treatment for cutaneous tumours.Information regarding different types of cancer will be obtained by including patients with tumours of any cancer histology.Procedures for calcium electroporation are clearly defined and tested in a multicentre setting.Calcium electroporation methods are thoroughly described in this protocol to facilitate clinical standardisation.This study is limited in size (30 patients).

## Introduction

### Clinical challenges of cancer affecting the skin

Skin manifestation of malignancy is a distressing problem for a significant number of patients with cancer. The area of disease can vary in size from a few millimetres to extensive areas of the body, and surgical or oncological management is often challenging. The tumours can develop in the last few months of life but some are present for years and often require palliative management.^1^ Calcium electroporation (CaEP) is a new, promising local treatment for cutaneous and subcutaneous malignancy.^2 3^

The following describes anticancer properties of calcium overloading using the electroporation technique and outlines preclinical discoveries as well as the first clinical experiences with CaEP for different types of solid tumours, before describing protocol design.

### Electroporation can be used to induce calcium overload

Electroporation is a method that can locally increase the intracellular concentration of otherwise non-permeant molecules. Application of short high-voltage pulses can create transient pores in cell membranes allowing molecules to diffuse in and out of targeted cells. The electroporation method can be used to increase the uptake of antineoplastic agents,^4–7^ nucleotides (ie, DNA/RNA)^8–10^ as well as non-permeant electrolytes such as calcium.^11–13^

### Effects on normal and malignant cells: preclinical studies

Calcium is a non-permeant ion involved in various cellular signalling processes such as gene transcription, proliferation, metabolism and apoptosis. Human eukaryote cells can restore calcium homeostasis by storing intracellular Ca^2+^ in cellular compartments, chelating Ca^2+^ to intracellular proteins and extruding Ca^2+^ from the cytosol (figure 1).

**Figure 1 F1:**
[figure not shown]
Schematic overview of known effects of calcium electroporation on normal cells and cancer cells. Electroporation pulse treatment creates transient pores in both cancer cells (bottom row) and normal cells (top row). In a high calcium concentration environment, the intracellular calcium level is greatly increased immediately after treatment. After a few minutes, the plasma membrane reseals and both normal and malignant cells are overloaded with Ca^2+^. Ca^2+^ extrusion from the cytoplasm is carried out by Na^+^-Ca^2+^ exchangers, plasma membrane Ca^2+^-ATPase pumps and sarco-endoplasmic reticulum Ca^2+^-ATPase pumps that transport Ca^2+^ into the extracellular space and into the endoplasmic reticulum lumen, respectively while consuming ATP in both normal and cancer cells. Suppression of free cytosolic calcium is further facilitated by buffering in mitochondrial compartments and binding to Ca^2+^-binding proteins. Calcium pumps and channels may be upregulated or downregulated in malignant cells, impairing calcium homeostasis. Furthermore, cancer cells can have weakened membrane repair mechanisms. Ca^2+^ overload induces mitochondrial dysfunction and critical ATP depletion in cancer cells. These properties may act as mechanisms of calcium electroporation-induced cell death. As illustrated, electroporation may also cause cellular swelling. Following calcium electroporation, normal cells have the ability to restore homeostasis, while cancer cells are prone to necrotise. Cancer cell necrosis leads to release of a danger signal as well as cell remnants that may induce a local and/or systemic immune response.

Tumourigenesis alters cell calcium homeostasis through upregulation and downregulation of calcium pumps and calcium channels, calcium storage compartments as well as changes in the cytoskeleton and membrane repair.^14^ As a result, induction of cell death in cancer cells can be observed following calcium overload (figure 1).^15–18^ Mitochondrial collapse, ATP depletion and ultimately promotion of necrotic cell death have been observed in cancer cells following CaEP in vitro and in vivo.^11 12 19^ A preclinical cell study demonstrated that increased extracellular calcium alone does not influence cells in terms of decrease of ATP and cell death.^11 12^

Preclinical studies have shown that CaEP is efficient in inducing cell death in vitro and in vivo across several cancer histologies including human breast, bladder, lung and colon cancer cell lines.^11–13 20 21^ Normal cells and tissues have been observed to be significantly more resistant to electroporation treatment than cancer cells and tissues in structured models.^13 21 22^

### CaEP follows the principles of electrochemotherapy (ECT)

ECT is a standard therapy for cutaneous metastases where electroporation is used locally to increase cellular uptake of bleomycin, an antineoplastic drug.^23 24^ ECT is well tested in treatment of different malignancies with both systemic and local administration of bleomycin. Bleomycin induces apoptosis in cancer cells when delivered by electroporation, and although the mechanisms through which calcium overload induces cell death differs from that of bleomycin (eg, necrosis), the clinical setup and pulse parameters used for ECT are applicable.^2^ CaEP is a local treatment where calcium is administered intratumourally after which electrical pulses are applied to the target area. Like ECT, CaEP can be used for treatment of primary or secondary skin tumours or ulcerating malignant wounds such as basal and squamous cell skin cancers, melanoma skin cancer, Kaposi’s sarcoma, breast cancer skin metastasis or head-and-neck cancer recurrence.^2 7 25–27^ The procedure is performed in either general or local anaesthesia depending on tumour location and size, as well as patient preference and institutional operating procedure.^28 29^

### CaEP for tumours affecting the skin and mucosa: clinical studies

The first small clinical trial using CaEP was designed as a double-blinded randomised study comparing ECT and CaEP.^2^ This study showed CaEP to be safe, efficient and non-inferior to ECT.

The trial included seven patients of which six had breast cancer and one had malignant melanoma. A total of 47 cutaneous metastases were treated of which 37 were randomised and evaluated for response and 10 were biopsied. A complete response (CR) was obtained in 66% (12/18) of calcium electroporated metastases versus 68% (13/19) of metastases treated with ECT.^2^

A second study with similar preset criteria included seven patients with cutaneous metastasis (six patients with malignant melanoma and one with breast cancer). The study supported the safety and effectiveness of CaEP. While a difference in rates of CR was observed between metastases treated with CaEP (22%) and ECT (40%), both rates were lower compared with the first small initial trial.^2 3^

Finally, CaEP was proven to be safe and efficient in a trial investigating CaEP for recurrent head and neck cancer (n=6) with a local response rate in treated lesions of 50%, which is comparable with those of ECT. CaEP had limited side effects, and one of the treated patients exhibited CR.^2 27^

### Purpose of this study

The first clinical trials have shown encouraging results.^2 3^ The purpose of this study is to investigate CaEP as an anticancer treatment in a larger cohort to aid the translation of this easily implemented treatment to a standardised clinical setting. This study will also encompass response evaluation by MRI and quality of life (QoL) analyses.

## Methods and analysis

### Design

This is a non-randomised, single-arm phase II trial. All patients will receive treatment, and CaEP will not be compared with other treatment modalities.

### Setting

This study will be carried out at three cancer centres in Northern Europe: Zealand University Hospital, Denmark; University Hospital of Southern Denmark; and University Hospital Schleswig-Holstein, Germany. The 3-year study period began on 11 February 2020.

### Participants

We seek to include 30 patients (10 at each site) with cutaneous malignancy of any type. Inclusion criteria in the trial are: (1) age older than 18 years of age; (2) ability to understand the participant information; (3) histologically verified cutaneous or subcutaneous cancer of any histology; (4) previously offered other relevant standard treatment for their cancer disease; (5) progressive or stable disease is present after a medical treatment period of 2 months or more (endocrine therapy, chemotherapy, immunotherapy, etc); (6) current radiation therapy does not involve the treated area; (7) performance status Eastern Cooperative Oncology Group (ECOG)/WHO ≤2; (8) at least one cutaneous or subcutaneous tumour measuring up to 3 cm; (9) if sexually active, use of safe contraception (contraceptive coil, deposit injection of gestagen, subdermal implantation, hormonal vaginal ring or transdermal patch); and (10) signed informed consent.

Exclusion criteria are pregnancy or lactation. Trial subjects are withdrawn from the study if the patient withdraws his or her consent; if disease progression requires new treatment strategies; and investigator deems that withdrawing is in the best interest of the patient.

### Primary endpoint

The primary endpoint is to evaluate the clinical response rate of CaEP treatment of malignant tumours of the skin at 2 months after treatment. Response rate will be defined as number of responding lesions (PR or CR) proportional to number of treated lesions, evaluated by changes in size (mm) clinically measured using a Vernier calliper. Tumour response will be documented using clinical photography. A maximum of seven tumours up to 3 cm in largest diameter will be treated and followed per patient.

Response will be evaluated according to the modified RECIST guideline^30^ and defined as: CR: disappearance of the lesion; partial response (PR): at least 30% decrease in the largest diameter of the lesion; progressive disease: at least 20% increase in the largest diameter of the lesion; and stable disease (SD): neither 30% decrease nor 20% increase of the largest diameter of the lesion.

### Secondary endpoints

The secondary endpoints include: (1) treatment response at months 1, 3, 4, 6 and 12; (2) tumour and surrounding tissue histopathological regressive changes (eg, % tumour cells and fibrosis) assessed by microscopy of biopsies taken from the treated area after 1 year; (3) response after treatment on MRI scans on a subset of patients before and immediately after treatment, as well as after 2 months using diffusion-weighted magnetic resonance imaging (DW-MRI) as a method to monitor electroporated tissue, using the apparent diffusion coefficient (ADC); (4) QoL before and after treatment using European Organisation for Research and Treatment of Cancer (EORTC) Questionnaires; (5) QoL before treatment, after 2 months and after 1 year through EORTC QLQ-C15-PAL Core questionnaires evaluating cancer-related symptoms on a scale from 1 to 4 (not at all to very much) as well as overall QoL on a scale from 1 to 7 (very poor to excellent); (6) observable systemic immunological response from any routine scans (MRI, PET-CT, etc) before and after treatment in the inclusion period by tumour size and Tumour Node Metastasis (TNM) stage; (7) response rates and response duration according to tumour histology; (8) complete and partial remissions of all treated tumours (defined as number of partially or complete responding lesions relatively); (9) rate of response for each individual patient; (10) response (overall, as well as complete and partial) depending whether the treated tumour was in a previously irradiated area; (11) current during treatment as measured by the pulse generator; and (12) qualitative interviews (in a subset of patients) performed before and 2 months after treatment that include measures related to patient experience and impact on QoL.

## Ethics, safety and dissemination

The trial will be conducted in accordance with the official version of the Declaration of Helsinki and in agreement with The International Council for Harmonisation of Technical Requirements for Pharmaceuticals for Human Use directions for Good Clinical Practice and the respective rules and regulations in Denmark and Germany.

As the treatment is safe and has not led to disease progression or increased tumour growth compared with controls in any preclinical or clinical studies, we expect CaEP treatment to be safe in treatment of cutaneous or subcutaneous malignant tumours of any histology.^2 3 11 13 21 22 25 26 31 32^ Adverse events and serious adverse events (SAEs) will be evaluated and graded according to CTCAE V.4.0. In view of the severity of metastatic cancer disease, there are certain conditions defined as SAEs but not reported as such in this study, for example, voluntary hospitalisation and surgery as treatment of the underlying cancer.

The trial is approved by the European Medicines Agency and Danish Medicines Agency and pending approval from relevant authorities in Germany. The trial is approved by the Danish Regional Committee on Health Research Ethics (Den Videnskabsetiske Komite for Region Sjælland), 13 December 2019 (case no: SJ-810), Data Protection Agency (no. REG-115–2019) and this trial was registered on EudraCT and ClinicalTrials.gov. Participation in the study requires signed informed consent. The study started on 11 Febuary 2020, and the first patient was included in the study on 18 February 2020. Data will be published in a peer-reviewed journal. Deidentified participant data are available from the corresponding author on reasonable request. Reuse of data requires approval from the pertinent ethics committee. The results of the trial will be made available to the public by open access publication followed up with summaries posted on institution websites and other publically accessible sources.

### Patient and public involvement

Patients and the public were not involved in the writing of the protocol in this study. A patient and public research panel will be engaged in the discussion of the outcomes of both response to therapy and the QoL analysis.

### Study process

#### Preoperative assessment

After consent and inclusion in the study, data concerning medical history including cancer diagnosis, TNM classification, past and ongoing treatments, demographic data, comorbidity, radiological data, pathology, clinical photos, ECGs, blood tests (including haemoglobin, blood cell count, serum-calcium and C reactive protein) and list of prescription medicine will be recorded. Relevant data will be stored on the case report form and on a clinical trial management system (EasyTrial ApS, Aalborg, Denmark).

#### Definition of treatment target and photography

The visible and/or palpable target area is assessed clinically and marked (figure 2).

**Figure 2 F2:**
[figure not shown]
Pretreatment and follow-up photography. Guide to overview photo of numbered target lesions (A) and photo of target lesion centrally in the image with longest diameter horizontally. Tumour marked proximally (violet) and adhesive ruler for scale 1 cm below the tumour at the bottom of the image (B). Tumours are numbered according to clinician preference, preferably with the most symptomatic tumour marked as tumour 1.

The treated areas will be photographed prior to treatment on day 0 and at follow-up 1, 2, 3, 4, 6 and 12 months after treatment. At each visit, an overview photo of the treatment sites will be taken, as well as photos of each target tumour (figure 2).

#### QoL assessment

Patient QoL is planned for evaluation before treatment, after 2 months and after 1 year, through using the EORTC-certified QLQ-C15-PAL Core Questionnaire. A subset of patients treated at Zealand University Hospital will participate in a qualitative interview at month 0 (before treatment), 2 and 12, in order to assess treatment impact on the QoL of patients with cancer treated with CaEP. The qualitative interview seeks to explore patients’ physical and emotional well-being before and after treatment as well as expectations and experience in relation to treatment. The interviews will be conducted as semistructured face-to-face interviews as well as phone calls, both based on interview guides.^33^ The recorded interviews will be transcribed and analysed to describe physical and emotional well-being experienced by the patients.

#### Anaesthesia

Paracetamol 1 g and/or lidocaine cream may be prescribed 1 hour preoperatively as a prophylactic analgesic for mild pain. CaEP will be performed using local anaesthesia with injection of lidocaine-epinephrine 1% peritumourally, although other anaesthesia may be used. A sufficient amount of local anaesthetics will be applied, which is comparative with other small local surgical procedures (figure 3).

**Figure 3 F3:**
[figure not shown]
Treatment area. Local anaesthetic applied peritumourally in a rhomboid manner in an appropriate distance from the target area. For a total tumour treatment, the aim is to treat all visible and/or palpable tumours with a 3 mm margin of clinically normal skin included in the target area. Blue-grey: anaesthetised area; rose: tumour; violet: target margin.

The maximum recommended dose of local anaesthesia will not be exceeded (30 mL for lidocaine-epinephrine 1%). The procedure may be performed in general anaesthesia and muscular relaxant administered, according to standard procedure of the institute. The equipment used in the CaEP procedure is described in figure 4.

**Figure 4 F4:**
[figure not shown]
Equipment for calcium electroporation. (A) Anaesthesia is necessary, either local anaesthesia or other (depending on tumour location and size). (B) Calcium is always administered by local injection and using, for example, 1 mL syringes ensures easy and steady administration. (C) Electric pulse delivery is performed by needle electrodes that can penetrate so that the bottom of the tumour can be covered. The linear array electrode is preferred due to superior results for smaller tumours. (D) A square wave pulse generator (electroporator) enables precise delivery of pulses of the planned treatment sequence, in this case eight pulses of 0.1 ms with a voltage of 400 V (corresponding to 1 kV/cm applied voltage to electrode distance ratio, as used for the linear array electrode).

#### Calcium dose and tumour volume

Participants will be given a maximum of 20 mL calcium solution of 220 mmol/L administered intratumourally, equalling a total calcium dose of 4.4 mmol. The calcium dose in this trial will be analogous to the first phase II trials testing CaEP on small cutaneous tumours.^2 3^ Ten millilitres of calcium chloride 500 mM is suspended in 12.7 mL isotonic NaCl solution to a calcium dose of 220 mmol/L. Mixing is performed bedside and countersigned by an observer. The dose to tumour volume ratio is an adapted calculation from the European Standard Operating Procedure of Electrochemotherapy (ESOPE) guidelines^23 29^: (1) tumour with a diameter <0.5 cm: 1 mL/cm^3^ tumour tissue; and (2) with a diameter from 0.5 cm to 3 cm: 0.5 mL/cm^3^ of tumour tissue.

Tumour volume will be calculated according to ESOPE by the following formula: *V=ab*
2
*π / 6* (*a*=the longest tumour diameter in cm; *b*=the longest diameter perpendicular to *a*).

It is important that the entire tumour volume and surrounding tissue is treated, thus we have chosen to define a treatment margin of 3 mm around the tumour when injecting calcium in the electroporation treatment area (figure 3). Calcium will be administered intratumourally by manual injection with linear application on needle retirement spaced around 5 mm to ensure an equal distribution of calcium in the tumour (figure 5). As the volume of peripheral tissue is infinitely variable (figure 6A–C), adequate volume of injected calcium chloride should be individually assessed by the treating clinician.

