**Figure 6 F6:**
[figure not shown]
Cancer location in skin layers. Tumours may present as subcutaneous or cutaneous and involve some or all skin layers, for example, subcutaneous fat (A), dermis (B) and/or epidermis (C). If the epidermis is involved, the tumours may present as ulcerating or fungating wounds. *Intact skin versus necrosis after CaEP*. In most cases, subcutaneous tumours (A) will not ulcerate after calcium electroporation, and skin will often appear intact after treatment. If treated tumours are situated as in figure part B, there may or may not be ulceration after treatment, depending on many factors such as patient healing potential and degree of invasion of the upper skin layers. Ulcerating or fungating tumours (C) may develop a necrotic, often crusted wound following treatment.

For practical purposes, a calcium solution (220 mmol/L) dose corresponding to half of tumour volume (mL) is distributed in the margin area. Due to differences in tumour situation in the cutaneous and subcutaneous layers, standardised dose of the tumour margin area can be a challenge (figure 6a–c). The intratumourally injected volume and total injected dose for each tumour are noted.

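### The 20 mL calcium cap, the 4.4 mmol total and the added margin volume do not agree, and for patients with several large lesions this leaves open which lesions enter the primary denominator

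*Protocol article*

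**What the plan says.** All references are to the Protocol article.

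- **Cap** (Calcium dose and tumour volume): "Participants will be given a maximum of 20 mL calcium solution of 220 mmol/L administered intratumourally". The article then converts that volume into an amount of calcium and presents it as the whole dose: "equalling a total calcium dose of 4.4 mmol".
- **Intratumoural rule** (same section): the smallest lesions, below 0.5 cm, get 1 mL per cm³. For the main size range the rule reads: "with a diameter from 0.5 cm to 3 cm: 0.5 mL/cm^3^ of tumour tissue". Volume comes from the two diameters by V = ab²π/6.
- **Margin rule** (same section, text after the Figure 6 legend): "a calcium solution (220 mmol/L) dose corresponding to half of tumour volume (mL) is distributed in the margin area". Intratumoural volume and total dose are noted separately for each tumour. The section also says of the variable peripheral tissue that "adequate volume of injected calcium chloride should be individually assessed by the treating clinician".
- **Safety argument** (same section): 4.4 mmol is taken as the maximum dose when the rise in systemic calcium is estimated. A few lines later, 40 mL of the same solution is described as safe.
- **Lesion allowance** (Primary endpoint): "A maximum of seven tumours up to 3 cm in largest diameter will be treated and followed per patient". The power section sets a minimum of one treated tumour per patient.
- **Primary endpoint**: responding lesions divided by treated lesions.

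**The concern.** The cap is worded for solution placed in the tumour, but it is then called a total and used as a total in the safety argument. The margin rule adds a second volume that is just as large for lesions of 0.5 to 3 cm. Only one of two things can be true. Either the margin calcium lies outside the cap, and 4.4 mmol is not the maximum that the rules allow; or it lies inside, and the cap is reached with few large lesions.

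Two things are at stake. The first is the maximum dose on which the article rests its systemic-calcium argument. The second is the primary endpoint. When calculated volumes reach the cap, someone must decide which lesions are treated, and treated lesions form the denominator. In a single-arm trial with three centres of differing electroporation experience and 24 expected evaluable patients, a few multi-lesion patients can weigh on a pooled lesion rate. A choice among their lesions made at the bedside is a route to bias.

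**Working it through.** **The plan's own figures.** Cap: 0.020 L × 220 mmol/L = 4.4 mmol, as stated. Mixture: 10 mL × 500 mmol/L ÷ 22.7 mL = 220.3 mmol/L, as stated.

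**Volume per lesion (0.5 to 3 cm).** Intratumoural = 0.5V. Margin = 0.5V. Total = V.

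For a round 3 cm lesion (a = b = 3): V = 3 × 3² × π/6 = 14.14 cm³, so 7.07 mL in the tumour, 7.07 mL in the margin and 14.14 mL in all.

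**Reading A: the cap covers intratumoural solution only.** With 20 mL in tumours, the margin rule adds another 20 mL. The total is 40 mL, and 0.040 L × 220 mmol/L = 8.8 mmol, twice 4.4 mmol. This is reachable, since it needs a combined tumour volume of 40 cm³ and seven round 3 cm lesions hold 7 × 14.14 = 99 cm³.

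**Reading B: the cap covers everything injected.** The total stays at 4.4 mmol, but the cap is met sooner.

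| Round 3 cm lesions | Intratumoural only (A) | Margin counted (B) |
|---|---|---|
| 1 | 7.07 mL | 14.14 mL |
| 2 | 14.14 mL | 28.27 mL (above 20) |
| 3 | 21.21 mL (above 20) | 42.41 mL |
| 7 | 49.48 mL | 98.96 mL |

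**Largest seven equal round lesions that fit.**
- B: (20/7 × 6/π)^(1/3) = 1.76 cm.
- A: (20/3.5 × 6/π)^(1/3) = 2.22 cm.

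**Sensitivity to shape.** With a = 3 cm and margin counted, two lesions need 2 × 3b²π/6 = πb² mL. This passes 20 mL only when b exceeds √(20/π) = 2.52 cm. Two lesions of 3 × 2.5 cm need 19.6 mL, and two of 3 × 2 cm need 12.6 mL. Seven of 3 × 2 cm pass the cap on both readings (22.0 mL under A, 44.0 mL under B). Seven of 3 × 1.5 cm pass it only under B (12.4 and 24.7 mL).

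**Where the cap does not bind.** Seven round 1.5 cm lesions need 12.4 mL with margin counted.

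**The safety figure.** Spreading 4.4 mmol over the stated 15 L gives 4.4/15 = 0.29 mmol/L, so 2.55 would become 2.84 mmol/L, where the text gives 2.66. That is a separate discrepancy, but it sits in the same paragraph and should be settled at the same time.

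**The case against.** **The limits are ceilings.** A reader might infer that the rules cannot all hold, so that lesions must be under-dosed or the cap broken. The documents do not support that. Twenty millilitres, seven tumours and 3 cm are all maxima, and only one lesion has to be treated. Treating fewer lesions at their calculated volumes meets every rule. The Figure 3 legend speaks of treating all visible or palpable tumour, but as an aim. This objection stands. What remains is the choice of which lesions are treated.

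**Two 3 cm lesions need not pass the cap.** A reader might state this as a fact. It holds only for near-round lesions and only if margin volume counts. On the literal intratumoural wording, two take 14.1 mL.

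**The margin text need not contradict itself.** Half the tumour volume is introduced as a practical figure, and the article admits that the margin is hard to standardise. This can be read as a default plus clinical judgement, so it is not pressed as a separate error.

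**An article leaves detail to the full protocol.** What to do when the cap is reached could well be set out there, and its absence alone would be no finding. The mismatch between the cap's wording, the 4.4 mmol total, the margin rule and the safety argument is different, because all four stand in the article.

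**The 40 mL remark might seem to settle the matter.** It equals the Reading A total, but the article does not link the two, and its concentration estimate uses 4.4 mmol.

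**Conclusion.** The point holds in limited form. The article does not say consistently what the 20 mL covers. On the literal wording the rules permit up to 40 mL (8.8 mmol), twice the stated total. If 20 mL is the total, round 3 cm lesions reach it at the second of seven permitted.

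The figures assume the stated volume formula, the half-volume margin rule applied as written and, for the counts of 3 cm lesions, a round shape. The seven-lesion totals of 49.5 and 99.0 mL are the extreme corner of the rules and not an expected case.

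The article gives no distribution of lesion number or size, so neither the share of patients affected nor the size or direction of any bias in the response rate can be estimated. Patients with few or small lesions are untouched. Severity is moderate: the passages should be reconciled because a safety figure rests on them, but the design does not fail on this point.

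**What to change.** 1. **Reconcile the text.** The sponsor should make the 20 mL cap, the 4.4 mmol total, the margin volume and the figures in the systemic-calcium paragraph agree, and state how the cap and the allowance of seven tumours up to 3 cm fit together. Which reading applies, and what yields when the cap is reached, is the sponsor's clinical decision; no dose or rule is proposed here.
2. **Fix the lesions in advance.** List in the CRF, before the first injection, the lesions to be treated and the calculated volume for each.
3. **Report what the cap excluded.** Report separately any eligible lesions left untreated because of the cap. Keep the primary denominator as treated lesions; counting untreated lesions in it would contradict the endpoint definition.

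The cost is a clarifying amendment and a CRF field. Injected volumes per tumour are already noted, and the calculated volume follows from the two diameters, so the sample size and visits do not change.
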